**10.0 RADIATION THERAPY**

Chemoradiation will be offered to patients with either pT3 or pN1 resected tumours. Resected pT1N0, pT2N0 patients will not be offered adjuvant therapy but will be followed and analyzed together in the experimental arm using the intention-to-treat principle.

Patients that haveR1 or R2 positive resection margins following induction chemoradiation will not receive adjuvant chemotherapy.

The total dose for both arms will be 50.4Gy (1.8Gy/fx/day), 5 days a week, prescribed to the periphery (95% isodose curve of the PTV.)

External Beam Equipment

Megavoltage equipment is required with effective photon energies >_ 6MV.

Treatment Planning – 3 D.

Treatment planning CT study will be required to define gross tumor volume (GTV) and

planning target volume (PTV). For this study, local regional nodes (whether clinically

positive or negative) will be included in the clinical target volume (CTV). Each patient will be positioned in an individualized immobilization device in the treatment position on

a flat table. The GTV and PTV and normal organs will be outlined on all appropriate CT

slices and displayed using beam’s eye view. Normal tissues to be contoured included both lungs, skin, heart, spinal cord, esophagus, kidneys, and liver. 4D-CT is allowed if applicable. VQ SPECT is optional. Patient immobilization is required. Patient may be placed in the supine or prone position.

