**7.1 Overview of Treatment Plan**

The control arm of this study will consist of induction chemotherapy (2 Cycles - Cisplatin plus continuous infusion of 5-Fluorouracil) and concurrent radiation followed by surgical resection of the esophagus. The experimental arm will consist of surgical resection followed by (if required based on final pathological staging) two cycles of chemotherapy (Epirubicin, Cisplatin and continuous infusion of 5-Fluorouracil) and concurrent extended volume radiation treatment with the last 2 cycles. Follow-up of patients with clinic visits of similar frequency to the experimental arm will be required to avoid introduction of bias in recording of time to progression.

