**8.2.5 Positive Resection Margins**

Patients that are found to have cancer positive proximal, or distal margins following preoperative chemoradiation and surgery should be considered for additional chemoradiation at the discretion of the medical and radiation oncologists. Patients in the experimental arm (postoperative chemoradiation) that were found to be T1-2 and N0 with positive resection margins should also be considered for postoperative chemoradiation.

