**Arm II: Postoperative Chemotherapy (Experimental Arm) QUINTETT-ADJ**

Treatment should begin between 8 to 12 weeks following surgery.

The chemotherapy treatment is as follows:

Chemotherapy alone for 2 cycles – One cycle consists of Epirubicin 50 mg/ m2 and Cisplatin 60 mg/m2 day 1, and 5-Fluorouracil (5FU) by continuous venous infusion at 200 mg/m2 for 21 days.

Chemotherapy (concurrent with radiation) immediately afterwards for 2 additional cycles – One cycle consists of Cisplatin 60 mg/m2 day 1, and 5-Fluorouracil (5FU) by continuous venous infusion at 200 mg/m2 for 21 days. Concurrent radiation is to start on the same day as cisplatin is administered if possible, but in all cases within 3 days before or after that date.

Details regarding the chemotherapeutic agents:

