**Surgery**

**Positive Resection Margins**

**Consider Chemoradiation**

**Clear Resection Margins**

Follow-up

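### Sections 8.2.5 and 10.0 of the protocol contradict each other on postoperative treatment for patients with positive resection margins, in both arms

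*Protocol*

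**What the plan says.** **Control arm, positive margins.** Protocol 8.2.5 (Positive Resection Margins) says that patients with positive proximal or distal "margins following preoperative chemoradiation and surgery should be considered for additional chemoradiation at the discretion of the medical and radiation oncologists". The Study Schema has a box for positive margins followed by "Consider Chemoradiation". Protocol 10.0 (Radiation Therapy) says that patients with R1 or R2 "positive resection margins following induction chemoradiation will not receive adjuvant chemotherapy".

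**Experimental arm, early stage with positive margins.** Protocol 8.2.5 says that patients "found to be T1-2 and N0 with positive resection margins should also be considered for postoperative chemoradiation". Protocol 10.0 says: "Resected pT1N0, pT2N0 patients will not be offered adjuvant therapy". It adds that these patients are still followed and analysed in the experimental arm by intention to treat. It mentions no exception for margins.

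**Number of adjuvant cycles (minor).** The overview in 7.1 describes "two cycles of chemotherapy (Epirubicin, Cisplatin and continuous infusion of 5-Fluorouracil) and concurrent extended volume radiation treatment with the last 2 cycles". Section 9.0, Arm II, describes two cycles of chemotherapy alone and then "Chemotherapy (concurrent with radiation) immediately afterwards for 2 additional cycles".

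**The concern.** The trial compares two sequences of surgery, chemotherapy and radiation, so what happens after surgery is part of what separates the arms. For margin-positive patients, one section leaves further chemoradiation open and another rules it out.

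Three features of the design make this more than an editorial matter:

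- Section 17.2 states that patients, investigators and analysts are not blinded, and 8.2.5 leaves the control-arm decision to the oncologists' discretion. Which section is followed may therefore vary with physician and with arm.
- FACT-E, the primary outcome, is collected at baseline and every two months for one year (11.1, 12.1). A further course of chemoradiation in that year can affect it, as well as toxicity, recurrence and cost.
- For the individual patient, additional chemoradiation is considered or withheld according to the page consulted.

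**Working it through.** **1. The margin rules side by side**

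| Patients | Section 8.2.5 | Section 10.0 | Study Schema |
|---|---|---|---|
| Control arm, positive margins after induction and surgery | Consider additional chemoradiation, at discretion | No adjuvant chemotherapy (R1 or R2) | Consider chemoradiation |
| Experimental arm, T1-2 N0, positive margins | Consider postoperative chemoradiation | No adjuvant therapy offered to pT1N0 or pT2N0; no margin exception | No separate rule legible |
| Experimental arm, pT3 or pN1, any margin | Not addressed | Chemoradiation offered | Consistent with 10.0 |

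In the first row, chemoradiation includes chemotherapy, so giving what 8.2.5 allows breaks 10.0. The two groups are not worded identically. Section 8.2.5 refers to proximal or distal margins, whereas 10.0 refers to R1 or R2, and 8.3.3 defines R2 by gross disease left behind. They overlap at least in R1 patients with tumour at or within 1 mm of a proximal or distal margin (8.3.3). In the second row, a pT1-2N0 patient with a positive margin meets both statements at once. In the third row there is no conflict.

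**2. How many patients**

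Inputs: 48 per arm (17.1), and a margin-positive rate r. The documents give no r, so 10-20% is an assumption.

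The plan's own figure reproduces: n per arm = 2 × 25² × (1.960 + 0.842)² / 15² = 43.6, rounded up to 44. Adding 10% gives 44 × 1.1 = 48.4, stated as 48.

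- Control arm: 48 × 0.10 = 4.8 and 48 × 0.20 = 9.6, so about 5 to 10 patients.
- Experimental arm: 48 × r × q, where q is the share of margin-positive patients who are pT1-2N0. The documents give no q. Unless every margin-positive patient is pT1-2N0, the number is below 4.8 to 9.6 at the same r. The rate r may also differ between arms, since only one arm has treatment before resection.

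**3. Cycle count**

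- 9.0: 2 + 2 = 4 cycles.
- 9.1.3: cisplatin on days 1, 22, 43 and 64, which is four starts 21 days apart.
- 9.2.4: four 21-day cycles of 5-FU; 4 × 21 = 84 days = 12 weeks, as stated there.
- 10.0, Arm II: radiation starts with cycle 3.

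These agree. The 7.1 sentence names two cycles and then places radiation in the last two. That can be made to fit only if the two named cycles are the epirubicin cycles (days 1 and 22 in 9.3.4) and two more follow unmentioned.

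**The case against.** **Section 8.2.5 only asks that treatment be considered.** A clinician could consider it, decline, and so satisfy 10.0. But then 8.2.5 could never lead to treatment and its discretion would be empty. The conflict stands.

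**In the experimental arm, 8.2.5 may be a specific exception to the general stage rule in 10.0.** This is the better defence. Section 10.0 itself recognises margins when it sets the dose to the anastomosis. That text, however, governs dose in patients already receiving radiation, not who is offered it, and the stage rule is unqualified. The exception has to be guessed, so this conflict is real but weaker than the one in the control arm.

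**Readings that go too far.** A reader might also infer the following, which the documents do not support:

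- *Two cycles in one place and four in another, affecting every adjuvant-treated patient.* Section 7.1 does not call two the total, carries no doses or days, and the detailed sections agree on four. It is an unclear overview sentence.
- *pT3N0 patients fall into both schema branches.* This rests on two labels in a flowchart whose layout is lost in the text available. Section 10.0 settles it by offering chemoradiation for either pT3 or pN1.
- *Postoperative chemoradiation in the control arm is a crossover forbidden by 21.0.* Further treatment after induction and surgery is not clearly the other arm's strategy, and 8.2.5 names no regimen for it.

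**Conclusion.** The protocol gives contradictory instructions on postoperative treatment for margin-positive patients. The contradiction is firm in the control arm. In the experimental arm it is narrower, confined to patients who are both pT1-2N0 and margin-positive. On an assumed 10-20% margin-positive rate, it reaches about 5 to 10 of 48 control patients and a smaller number in the experimental arm.

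One might conclude that the two strategies as a whole are not fixed, or that 5 to 10 patients are affected in each arm. Neither follows. Sequence, drugs, the four-cycle regimen and the main pT/pN rule are stated, and margin-positive pT3 or pN1 patients in the experimental arm face no conflict. Assignment by intention to treat and the sample-size arithmetic are untouched. With no margin-positive rate and no effect of the additional treatment on FACT-E in the documents, no loss of power can be calculated.

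The point still merits correction, because it bears on patient safety and on an unblinded comparison, and because the correction is cheap.

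**What to change.** - Reconcile 8.2.5, 10.0 and the Study Schema into one rule per arm for margin-positive patients. Use one definition of the group (proximal or distal margin, R1, R2), and say explicitly whether the pT1-2N0 rule in 10.0 has a margin exception. Which rule stands is for the clinical leads; this review takes no view.
- Record any postoperative chemoradiation given in the control arm as a named treatment variable and report it by arm. State whether it counts as protocol treatment or as a deviation.
- As a minor point, align the 7.1 overview with the cycle description in 9.0, 9.1.3, 9.2.4 and 10.0.

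The cost is one text amendment and one item on the treatment form, with no new patients or procedures. Parts of 17.1 and 17.2 are written in the past tense. If treatment has already been delivered, the equivalent step is to state which rule was applied and report its use by arm.

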**Arm I: Preoperative Radiation Therapy (Control Arm)**

Radiation treatment will begin concurrent with chemotherapy cycle 1. Chemotherapy should start simultaneously with the first day of radiation treatment if possible, but in no circumstance later than day 5 of radiation treatment, and not earlier than on the first radiation treatment day.

The treatment planning target volume will be defined as per RTOG - 0113 with minimum modification. For mid-esophageal primaries (at or below the carina), the paraesophageal nodes need to be included-not the supraclavicular or celiac. For distal/gastroesophageal primaries, the field the celiac nodes should be included.

Barium swallow during the planning CT is optional provided a diagnostic chest was done with contrast to delineate the outline of the esophagus.

Target volumes

The Gross Tumor Volume (GTV) is defined as all known gross disease as defined by the planning CT and clinical information. Gross tumor includes the primary tumor (GTV-P) only. For the present protocol we have chosen to define the CTV a minimum of 4 cm proximal and distal and 1 cm lateral beyond the GTV delineated by CT scan and /or endoscopy. The final CTV may be larger for distal primaries since celiac nodes need to be included. The Planning Target Volume (PTV) will provide margin around the CTV to compensate for variability in treatment setup, breathing, or motion during treatment. The PTV volume must include 1cm around the CTV. The final superior and inferior margins will be approximately 5 cm beyond the GTV, and the lateral, anterior, and posterior margins will be approximately 2 cm beyond the GTV. If 4D-CT is used, IGTV (combinations of GTVs from full inspiration and expiration phases) should be determined. The IPTV will be 0.5cm around the ICTV.

Treatment Plan

3D Conformal Planning

Three-dimensional coplanar or non-coplanar beam geometry will be custom designed for each case to deliver highly conformal prescription dose distributions. The isocenter is defined as the common point of gantry and couch rotation for the treatment unit. The treatment plan will be composed of multiple static beams or arcs. The plan should be normalized to a defined point within the PTV. The PTV should be covered by the 95% isodose line with minimal hotspots (105%).

An example of a 3D-Conformal plan is to initially treat the PTV with a parallel opposed (AP/PA) geometry, followed by obliques to exclude the spinal cord.

Phase I 39.6Gy/ 22fx (1.8Gy/fx)

The superior and inferior margins of the PTV will be approximately 5 cm beyond the GTV, the lateral, anterior, and posterior margins will be approximately 2cm (except vertebral body posterior will be on the bony surface) beyond the GTV. For the distal primaries, the celiac nodes need to be included. Radiation fields arrangement can be APPA or multiple.

Phase II 10.8Gy/6fx (1.8Gy/fx)

Same PTV volume as in phase I but radiation fields will oblique off the spinal cord. Radiation field arrangement can be multiple to come off the cord and other critical organs.

Intensity Modulated Radiation Therapy (IMRT)

IMRT is allowed in this study and should be considered only when target coverage, OAR dose limits, or dose spillage are not achievable with 3D conformal planning. IMRT plans should follow the same planning principles as for 3D conformal planning. The number of segments (control points) and the area of each segment should be optimized to ensure deliverability and avoid complex beam fluences.

A single phase of 50.4 in 28 fractions (1.8 Gy. /fx) will be sufficient.

**Arm II: Postoperative Radiation Therapy (Experimental Arm)**

Radiation treatment will begin with chemotherapy cycle 3. Concurrent radiation is to start on the same day as cisplatin is administered if possible, but in all cases within 3 days before or after that date.

Treatment planning target volume as per Yu, et al, (26) and Yu, et al (27), with minimum modification.

Target volumes

For the present protocol in post –op patients there is no GTV unless with residual disease and it should be delineated with surgical clips. GTV-P is defined as pre-op gross tumor volume as above. CTV should include the tumor bed and the anastomosis. The CTV will be 1 cm proximal of the anastomosis, 4 cm distal and 1 cm lateral, anterior, posterior beyond the pre-op GTV-P delineated by CT scan and /or endoscopy. For distal primaries celiac nodes (around T12 L1) should be included in the treatment fields.

Planning Target Volume (PTV) will provide margin around the CTV to compensate for variability in treatment set up, breathing, or motion during treatment. A margin of 1 cm around the CTV will define the PTV.

The final PTV superior margin will include the surgical anastomotic site (labeled with radio-opaque clips) proximally with 2 cm. The inferior margin of the field will be 5 cm beyond the pre-op GTV-P location. Lateral, anterior, and posterior borders will be 2 cm beyond the borders of the tumor bed and regional lymph nodes. Peri-esophageal lymph nodes will be included. A barium swallow or radio - contrast such as Esophocat® (preferred) may be obtained at the time of simulation to confirm the post -op location of the esophagus and stomach.

Treatment Plan

3D Conformal Planning

Phase I 30.6Gy/17fx (1.8Gy/fx)

The superior margin of the PTV will include the surgical anastomotic site (labelled with radio-opaque clips) proximally with 2 cm. The inferior margin of the field will be 5 cm beyond the previous GTV-P location. Lateral, anterior, and posterior borders will be 2 cm (except vertebral body posterior will be on the bony surface) beyond the lateral borders of the tumor bed and regional lymph nodes. For the distal primaries, the celiac nodes (around T12 L1) need to be included. Peri-esophageal lymph nodes will be included. Radiation fields arrangement can be APPA or multiple.

Phase II 19.8Gy /11fx (1.8Gy/fx)

This is the coned down field to include the pre-op GTV-P bed only. The PTV-P is 5 cm proximal and distal from pre-op GTV-P. The lateral, anterior, and posterior margins will be approximately 2 cm (except vertebral body posterior will be on the bony surface) beyond the pre-op GTV-P.

Radiation fields arrangement can be multiple to come off the cord and other critical organs.

The surgical anastomotic site should receive 30.6 Gy in 17 fractions if it is not involved with disease. It should be boosted to a maximum total dose of 50.40 Gy in 28 fractions if it is close or positive margins (together either within or outside the preop GTV-P at the discretion of the treating physician).

IMRT Planning

IMRT treatment planning is permitted. Should IMRT be the treatment planning choice, 36-38 Gy/ 28 fx is to deliver to include the anastomosis and 50.4Gy/28fx is to deliver to include the tumor bed (PTV-P) only.

Normal Tissue Volume and Tolerances.

The following organs and doses by volume are guidelines for the 3D treatment plan. All normal tissues assume treatment at 1.8 Gy/fx.

Lung V20 <30% (TL-GTV), V20 <35% (TL-PTV)

Spinal Cord 10cm < 46Gy; 20cm <40Gy

Heart 1/3< 45Gy, 2/3< 40Gy, 3/3< 35Gy

Liver 1/3<40Gy, 2/3<30Gy, 3/3< 25Gy

Kidney 1/3 < 40Gy, 2/3 < 25 Gy, 3/3 < 15 Gy

Stomach 1/3< 60Gy, 2/3 < 50 Gy, 3/3 < 45Gy

Esophagus 1/3 < 60Gy, 2/3< 55Gy, 3/3 < 50Gy

Medical physicist, [name] may be contacted for additional information regarding radiation planning techniques and resources.

Therapy Interruptions

If interruption of therapy (up to two weeks) becomes necessary, radiation therapy should be completed to the prescribed doses. Total number of fractions and elapsed days should be carefully reported. If an interruption of more than 2 weeks is necessary, resumption of treatment is at the discretion of the radiation oncology chair. The patient will be considered a major deviation, but follow-up will be continued.

Criteria for Toxicity.

Acute and late toxicity related to radiation therapy include fatigue, myelosuppression, skin erythema, subcutaneous fibrosis, esophagitis, carditis, myelitis, acute radiation pneumonitis and late pulmonary fibrosis, and esophageal stricture. Acute toxicity monitoring: Acute (<- 90 days from RT start) side effects of radiation therapy will be documented using the revised NCI Common Toxicity Criteria, version 3.0 (any more recent ones?).

Later toxicity monitoring. Late (> 90 days since RT start or persisting beyond 90 days) post-treatment complication will be evaluated and graded according to the RTOG Late Effect Radiation Morbidity Criteria.

**11.0 Outcomes**

**11.1 Primary Outcome**

**Quality-of-Life** Quality-of-Life as measured by the FACT-E over 1 year from randomization.

**11.2 Secondary Outcomes**

**11.2.1 Survival at 5 years.** All patients will be followed every 3 months for 2 years and then every 6 months up to 5 years or until death if it occurs before 5 years. Survival will be measured from randomization.

**11.2.2 Disease Free Survival.** Recurrence rates in the two groups including local (gastric or esophageal bed), regional (regional lymph nodes), and distant recurrences (supraclavicular lymph node, liver, peritoneal carcinomatosis, or lung, brain, etc.) will be compared. Disease free survival will be measured as the time from patient entry onto study until the first malignant disease recurrence.

**11.2.3 Site of Treatment Failure.** The location of the first site of malignant disease recurrence will be recorded. Local failure occurs within the gastric or esophageal bed, or regional lymph nodes. Distant failure occurs in the supraclavicular lymph nodes, liver, peritoneal carcinomatosis, pleura, lung, bones, brain, or elsewhere not considered local.

**11.2.4 Toxicities**. Possible adverse drug or radiation events will be reported as described in the London Regional Cancer Program Patient Assessment Record (PAR).

**11.2.5 Completeness of Resection.** The number of R0, R1, R2, and unresectable patients will be compared.

**11.2.6 Economic Evaluation.** Within the clinical trial we will also conduct an economic comparison of the two treatments. In summary, the viewpoint of the economic study will be that of a Provincial Ministry of Health and we will therefore document all direct health care costs associated with the treatment strategies over the 5-year period of follow-up. Case report forms will be designed to document physical items of resources consumed (i.e., tests, procedures, hospital stay) and unit prices will be estimated for resources using cost-accounting methods. In a circumstance where one of the tri-modality therapies is both more costly and more effective (i.e., greater number of QALYs) we will calculate the incremental cost per QALYs as the ratio of the difference (treatment minus control) in cost to the difference in QALYs. Incremental cost per QALYs estimates will be presented with associated 95% confidence intervals estimated by a resampling technique known as bootstrapping. To further explore uncertainties in the data and analysis we will also conduct extensive sensitivity analyses. We will attempt to project, using available data, costs, and outcomes to 5 years to ascertain whether the economic appraisal is sensitive to the time horizon of analysis.

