**3.2 Secondary Objectives**

3.2.1 To assess and compare the toxicities and morbidities of each approach.

3.2.2 To compare overall survival rates between the two treatment arms.

3.2.3 To compare recurrence in the two groups including local (gastric or esophageal bed), regional (regional lymph nodes), and distant recurrences (supraclavicular lymph node, liver, peritoneal carcinomatosis, or lung, brain, etc.).

3.2.4 To conduct an economic analysis comparing the two treatments.

3.2.5 To compare the proportion of complete (R0), microscopic positive (R1), and grossly positive (R2) resections between treatment arms.

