**8.3 Surgical Quality Assurance**

**8.3.1 Completeness of Resection:** All pathology reports from patients in the study will be reviewed. Reports must contain information about gross and microscopic contamination of surgical resection margins. Tumour measurements must be recorded at surgical resection.

**8.3.2 Curative (R0):** Resections are defined as curative (complete resection: R0) when all gross disease has been removed, and microscopic examination reveals all surgical margins free of tumour, i.e., pathological stage T1-3, N0-1, M0 resected. Resections will still be considered curative if pathologic examination reveals positive lymph nodes if the gross nodes were completely resected.

**8.3.3 Palliative (R1 and R2):** Palliative resection (incomplete resection: R1 or R2) will be considered to have taken place when gross disease has been left behind (R2), or when microscopic examination reveals surgical margins which are not free of tumour (R1). Positive margins are defined as tumour at or less than 1 mm from the proximal or distal margins.

**8.3.4 No resection:** The primary tumour could not be removed.

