**17.2 Statistical Analysis**

Descriptive statistics were generated for all patients and stratified by treatment arm for baseline patient, tumour and treatment characteristics and stratified by treatment arm for HRQOL endpoints stratified by follow-up visit, compared using the chi-square test, Fisher’s exact test, two-sample t-test, Wilcoxon rank sum test or paired t-test (compared to baseline only) as appropriate. Univariable Cox proportional hazards regression was performed for OS and DFS for all eligible variables for all patients (Supplemental Table 1 online). Kaplan-Meier estimates were generated for OS and DFS for all patients and stratified by treatment arm compared using the stratified log-rank test stratified by clinical nodal status (N0, N1). All statistical analysis was intention-to-treat and performed using SAS version 9.4 software (SAS Institute, Cary, NC, USA) using two-sided statistical testing at the 0.05 significance level. The trial was not powered to detect differences in the secondary outcomes including survival. There was no imputing, deletion, guessing, or substitution used for missing values. There were no interim analyses. There was no blinding of patients, investigators, or data analysts to the treatment allocation.

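### Disease-free survival counts only recurrence, so deaths without recurrence are not events and patients never made disease-free have no clear event; the curve is time to recurrence under another name

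*Protocol*

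**What the plan says.** Protocol 11.2.2 defines the endpoint: "Disease free survival will be measured as the time from patient entry onto study until the first malignant disease recurrence". The only events named there are recurrences, split by site: "Recurrence rates in the two groups including local (gastric or esophageal bed), regional (regional lymph nodes), and distant recurrences". No other section of the protocol defines DFS or adds death to it.

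Section 17.2 gives the analysis: "Kaplan-Meier estimates were generated for OS and DFS for all patients and stratified by treatment arm compared using the stratified log-rank test", and "Univariable Cox proportional hazards regression was performed for OS and DFS for all eligible variables for all patients". All analyses are by intention to treat. No competing-risk method is named.

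Section 8.3 recognises patients who are never made disease-free: R2 resection, where gross disease remains, and no resection, described as "The primary tumour could not be removed". Section 11.2.5 compares their numbers between arms. Section 11.2.2 gives them no DFS event.

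On sites of failure, 3.2.3 uses three categories: "local (gastric or esophageal bed), regional (regional lymph nodes), and distant recurrences". Section 11.2.2 does the same, but 11.2.3 states: "Local failure occurs within the gastric or esophageal bed, or regional lymph nodes".

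**The concern.** DFS is normally read as the chance of being alive and free of disease. With recurrence as the only event, a patient who dies of surgery, toxicity or another cause before recurring leaves the Kaplan-Meier analysis as a censored observation, as if recurrence could still be seen later. The resulting figure is not DFS.

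The clock also starts at study entry, when every patient has tumour in place. Someone whose tumour progresses before surgery, cannot be removed, or is only partly removed has nothing that can plainly be called a recurrence. The plan does not say whether or when that patient has an event.

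The arms place surgery at different times. Controls have chemoradiation first; experimental patients have surgery first. Deaths without recurrence and never-disease-free patients could therefore differ between arms in number or timing, and a recurrence-only comparison would not show it.

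The site wording adds a smaller problem. A regional nodal relapse is regional under 3.2.3 and 11.2.2 but local under 11.2.3. Section 1.0 uses reduced local recurrence to support the extended radiation volume, so the local failure rate should not depend on which paragraph is followed.

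**Working it through.** **The plan's own figures.** The protocol states no event count, hazard ratio or power for DFS, so there is no DFS figure to reproduce. The arm size used below comes from section 17 and concerns FACT-E: 2 × 25² × (1.960 + 0.842)² / 15² = 43.6, rounded up to 44; 44 × 1.1 = 48.4, stated as 48. It reproduces.

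**Direction of the error in level.** Let R be the recurrence-only Kaplan-Meier curve (deaths censored) and C the curve for recurrence or death. Both have the same patients at risk at every time. C is multiplied by every factor in R and by a further factor below 1 at each death without recurrence. So C can never lie above R, and it lies below R from the first such death onward. This needs no assumed rate.

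**Number of patients.** Section 1.0 cites 6.7% post-operative death from a meta-analysis of preoperative chemotherapy. Used only as an illustration, 0.067 × 48 = 3.2, or about 3 patients per arm.

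**Size of the error in level.** Assume constant hazards: recurrence λ = ln 2 / median, and death without recurrence μ = 0.06 to 0.10 a year (0.0050 to 0.0083 a month). The death rates are assumptions; the protocol gives none. Then R(t) = exp(−λt) and C(t) = exp(−(λ+μ)t). Two medians are shown:

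- 24 months is assumed, close to the 25-month median time to recurrence in one adjuvant series cited in 1.0.
- 10.4 months is the midpoint of the 10.2 and 10.6 months DFS in the trial group's own node-positive series in 1.0.

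| Median | λ per month | Time | R | C at 6% to 10% a year | Gap (points) |
|---|---|---|---|---|---|
| 24 months | 0.0289 | 12 months | 70.7% | 66.6% to 64.0% | 4.1 to 6.7 |
| 24 months | 0.0289 | 60 months | 17.7% | 13.1% to 10.7% | 4.6 to 7.0 |
| 10.4 months | 0.0667 | 12 months | 44.9% | 42.3% to 40.7% | 2.6 to 4.3 |
| 10.4 months | 0.0667 | 60 months | 1.8% | 1.4% to 1.1% | 0.5 to 0.7 |

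**If 1 − R were read as the proportion recurring.** The cumulative incidence is λ/(λ+μ) × (1 − C). At the 24-month median and 60 months, 1 − R is 82% while the cumulative incidence is 74% to 69%.

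**Effect on the comparison.** Assume a control median of 20 months (λ = 0.03466) and yearly risks p of death without recurrence, with μ = −ln(1 − p)/12. The hazard ratio for recurrence or death, experimental over control, is (HR × λ + μE)/(λ + μC).

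- Recurrence HR 1.00; 5% control, 10% experimental: (0.03466 + 0.00878)/(0.03466 + 0.00427) = 1.12. With the rates reversed: 0.90.
- Recurrence HR 0.80; 10% in both arms: (0.02773 + 0.00878)/(0.03466 + 0.00878) = 0.84.
- Recurrence HR 1.00 with equal rates: 1.00, so no distortion.

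These cases show that the comparison can move either way or not at all.

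**The case against.** Four objections have force.

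First, a reader might infer that the definition biases the comparison, for instance because progression before surgery would be missed mainly in controls. The documents do not support that as a fact. They give no arm-specific rates of death without recurrence, R2 resection or non-resection. Both arms have surgery, unresected or R2 cases could arise in either, and the 6.7% figure is cited together with a finding of no difference in post-operative death. Possible distortion is as far as one can go.

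Second, a reader might say that toxic or surgical deaths improve an arm's curve. They do not. A censored death fails to lower the curve; under independent censoring the recurrence curve is unchanged in expectation. The fault is that this curve is not DFS.

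Third, the protocol never says that deaths are censored; this follows from combining 11.2.2 with 17.2. Nor is it settled that R2 or unresected patients stay event-free, since later liver or lung disease could be recorded as distant recurrence. For them the definition is ambiguous.

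Fourth, the size depends on the chosen rates and is small at 5 years when recurrence is fast. DFS is also secondary and unpowered, section 21.0 treats the other secondary outcomes as hypothesis-generating, and overall survival captures every death.

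All four limit the claim. None removes the defect: the stated event omits death, and no other section repairs it. An unseen analysis plan does not help, because the protocol has already fixed the definition.

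**Conclusion.** The definition is wrong as written and should be changed. Following 11.2.2 and 17.2 produces a time-to-recurrence analysis reported as DFS. The level is overstated whenever a patient dies without recurrence; that direction is certain. The size is not: over the constant-hazard cases shown it runs from under 1 point to about 7 points, and it rests on an assumed 6-10% yearly rate of death without recurrence and the assumed median. Distortion between arms is possible, with direction and size that cannot be found from the document. The handling of R2, unresected and pre-surgery progression cases is undefined. The local/regional conflict is a separate, minor inconsistency; because the first site is recorded, either grouping can be derived.

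**What to change.** - In 11.2.2, define the DFS event as the first of recurrence or death from any cause, timed from randomization, as 11.2.1 already does for survival.
- Count R2 resection, no resection, or progression preventing resection as events under one dating rule used identically in both arms, for example the same fixed time from randomization. Dating them at surgery would place them later in the control arm merely because induction comes first.
- If recurrence alone is wanted, report it by site as cumulative incidence with death as a competing event.
- Reconcile 11.2.3 with the three-way split in 3.2.3 and 11.2.2.

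**Cost.** Definition wording and one extra analysis. Deaths (12.2), resection status (11.2.5) and first site of recurrence (11.2.3) are already recorded. Progression before surgery may be less completely captured: 8.2.1 requires a preoperative evaluation but does not say whether it is repeated after induction, so the source of that information should be stated. DFS figures will look slightly less favourable. The FACT-E analysis and the sample size do not change.
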